**Natural History of Smoking & Quitting: Longterm Outcomes**

**A. Specific Aims**

At present, some 50 million Americans smoke, these individuals are routinely encouraged to quit, and millions try to quit each year. A great deal is known about how quitting smoking affects a limited set of outcomes. For instance, it is well known that cessation affects the likelihood of lung cancer and heart disease. However, our knowledge of the effects of cessation is narrow. There are major gaps in our understanding of how cessation affects disease processes, mental health, psychosocial adjustment and life satisfaction. Also, little is known about the potential costs or adverse impacts of cessation. Finally, little is known about the precipitants of late relapse. The proposed research is aimed at addressing these gaps in our knowledge. Our cardinal goals are:

*1. To determine the effects of cessation and continued smoking on physiological mechanisms of cardiovascular disease*. We will use state-of-the-art assays such as carotid intima-media thickness, brachial artery endothelial function, and advanced lipoprotein testing to identify the mechanisms via which cessation leads to reduction of cardiovascular disease. We hypothesize that cessation will be followed by an arrest or reversal of atherosclerosis, but that this benefit will also be influenced by other modifiable risk factors (e.g., weight gain, diet, sedentariness, high stress). Our transdisciplinary assessment plan will allow us to produce new knowledge on the impact of cessation on atherosclerosis, and how cessation exerts its effects.1-8

*2. To determine the relation between cessation and mental health outcomes*. While cessation may exacerbate psychiatric symptoms in the short run (e.g., increased depression in the first year post-quit) we hypothesize that, over time, it will lead to decreased symptoms and a reduced likelihood of psychiatric diagnosis. These benefits may occur because smoking per se is a stressor9 because opponent-processes oppose the euphorogenic effects of nicotine10 or for other reasons. In sum we believe that our data will show that quitting smoking is the best thing that people can do to improve their mental health.

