Importantly, we now have highly quantifiable measures (e.g., Carotid IMT) that can, in an accurate and reproducible manner, document atherosclerotic progression or regression. These measures document the anatomical basis for the cardiovascular benefits of smoking cessation reported in epidemiologic studies.40-42 Such measures will also permit insight into the mechanisms of health outcomes, interactions among risk factors, and the subpopulations most affected by particular outcomes. Specifically, we need to know more about how cessation’s relation to atherosclerosis is influenced by individual differences such as gender, level of nicotine dependence and genotype43 and how cessation’s impact is related to changes in other modifiable risk factors such as diet, weight gain, exposure to environmental tobacco smoke, and exercise, which themselves may be affected by cessation.44 For instance, cessation induced weight gain might increase the risk of hypertension, insulin resistance, and hyperlipidemia, all important risk factors for atherosclerosis. Some data do address the impacts of such risk factors,45 but most data in this area are from cross-sectional or short-term cohort studies.1,21,29-32,46,47 Thus, measures such as Carotid IMT and flow-mediated vasodilatation of the brachial artery have rarely been studied prospectively with rich measures of individual differences and other risk factors.

While earlier data on cessation’s impact on carotid IMT showed *arrest* of carotid IMT over three years,1 we believe that more careful assessment of other risk factors may reveal *regression*. Such data have the potential to induce clinicians to change fundamentally their practice patterns. For example, data documenting the arrest of atherosclerotic progression resulting from hyperlipidemia has been associated with an explosive increase in the rate of prescribing statin agents.31 If tobacco cessation produces similar results, clinicians may be motivated to treat tobacco dependence more consistently and intensively. Of course, such data may also motivate more smokers to quit – pictures of atherosclerotic pathology and its arrest due to cessation could powerfully affect smokers’ motivation to quit.48 By integrating prospectively data on changes in smoking habits as well as other key risk factors and objective measures of atherosclerosis, we hope to clarify mechanisms and identify those at greatest risk.

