All logistic regression models will be developed and tested using procedures and recommendations of Hosmer & Lemeshow.277 For instance, variable selection will start with a careful univariate analysis of each variable, and computation of smoothed scatterplots for continuous variables. After univariate analyses, all independent variables with P-values <0.25 will be candidates for multivariate analyses. Subsequent variable selection will occur in the context of forward selection with a test for backwards elimination. Subsequent to the identification of a multivariate logistic model, the performance of each variable will be evaluated via inspection of the Wald statistic, and the comparison of the multivariate and univariate errors and regression coefficients. If a new model is generated this will be compared with the larger former model via the likelihood ratio test. Eliminated variables will be re-entered to ensure that they have not become valid predictors through the exclusion of other variables. The performance of all continuous variables will be tested for linearity of the logit and any hypothesized (*a priori*) interactions tested. Model fit will be assessed via the Hosmer-Lemeshow test and via area under the ROC curve. Standard model diagnostics will be used (e.g., inspection of leverage values, variance of residuals for covariate patterns). Construction of multiple regression models will be similarly standardized and subjected to appropriate diagnostics.280

Model building will follow strategies frequently used in longitudinal research.1 Thus, *control variables* will be routinely entered (e.g., gender, age, site, ethnicity, Project 1 treatment, SES). Change will be modeled via entry of pretreatment (baseline) measures of the dependent variable and via change scores (which protect against interpretive biases of partialled scores.281,282 Next, relevant *individual differences* will be entered: e.g., nicotine dependence, personality, and genotypes, depending upon the analysis. Then other *modifiable risk factors* will be entered: i.e., measures of diet, alcohol use/abuse, weight/BMI/waist circumference, stressors/distress, exercise, blood pressure, serum lipids, and exposure to second hand smoke. Principal relations will be presented both in univariate and multivariate models. Two-way interactions to be tested will be based upon a priori hypotheses for each tested model.

*Principal Hypotheses*

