Hypothesis 1: Smoking cessation (amount of abstinence over the follow-up period coded either dichotomously or continuously) will be associated with *reversal or arrest of atherosclerosis* as assessed via CIMT. Baseline CIMT scores will be used to determine change. *Individual differences and control variables*: Progression will be greater among males283,284 and among those high in trait (MPQ) Negative Emotionality.2,4,8 The following *modifiable risk factors* will predict greater atherosclerotic progression: weight gain, fat intake,1 BMI, second-hand smoke, sedentariness, and high levels of stress (e.g., 5-7). Exercise/activity, however, will predict greater regression. Two critical interactions with smoking will involve second-hand smoke and gender since research suggests different impacts of smoking depending upon these variables.1,283

Hypothesis 2. Smoking cessation/reduction will be associated with positive changes in *mental health functioning* (from baseline status). Change will be measured from either baseline (lifetime) history of diagnosis, or baseline symptom levels, depending upon the analysis. While cessation may initially increase depression/depressive symptoms, long-term cessation will be associated with improved mental health status as reflected by lower rates of psychiatric diagnoses and reduced symptoms (thus, some analyses will focus on Year 2 and 3 symptoms/diagnoses). *Individual differences and control variables*: post-cessation symptoms will be positively related to trait (MPQ) Negative Emotionality and female gender (especially if diagnoses are restricted to internalizing disorders) and severity of prequit nicotine dependence. *Modifiable risk factors*: mental health symptoms/diagnoses will be inversely related to post-quit social support and physical health, and positively related to post-quit stressor occurrence and frequency of postquit heavy drinking days (relevant to dependent variables that do not themselves comprise alcohol diagnoses). No interactions are predicted for this family of analyses.

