Figure 5 depicts an example of a multivariate unconditional latent trajectory model (LTM) for exploring alcohol use and smoking (modeled with only 4 repeated measures). Such models might also be used to explore relations between smoking and psychiatric symptoms, and between smoking and weight gain. Control variables such as those described in the “Predicting Discrete Endpoints” will be used as exogenous variables (MPQ Constraint, Gender, and Smoking in the Social Network). One exemplar set of predictions (Figure 5) would be that Gender will influence both initial drinking and smoking indices (Intercepts) with males showing higher levels. Low levels of trait Constraint would predict high initial smoking and drinking, and predict high levels of smoking over time. Post-quit smoking in the Social Network would also predict a reduced decline in smoking over time. Smoking and drinking might be inter-related in that higher smoking intercepts predict reduced declines in drinking over time.

Power

After accounting for relapse and attrition (initial N=900), we expect that data for at least 300 continuously abstinent and 450 smoking participants to be available for analysis. These estimates are based on the expectation that approximately 9% of the participants enrolled in Project 2 will either relapse (approximately 4% per year) or drop out of the study (approximately 5% per year) in years 2 and 3. The large number of primary and secondary hypotheses precludes presentation of power estimates for all possible comparisons. Two power analyses are presented below of central, discrete endpoint hypotheses.

*Long-term smoking status and atherosclerotic progression:* The best relevant estimates of CIMT effect sizes were reported by Howard et al.1 These authors analyzed CIMT change over a 3-year period in terms of smoking status (current, past, never) and ETS exposure. Howard et al.1 used mean common CIMT as the measure of progression (CIMTmean ). The authors computed linear regression models that controlled for demographic, life-style, and other risk factors and found a significant difference between current and past smokers of 7.3 m, equivalent to a 20% difference in progression.

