## In the current study, we will use a more sensitive measure of carotid IMT (CIMTmax ) that averages segmental maximum carotid wall thicknesses from all measurable carotid artery segments (up to a maximum of six segments). Bots et al.288 recommended CIMTmax for intervention trials and also computed pooled estimates of the annual rate of CIMT change across multiple atherosclerosis trials. These pooled estimates were then used to compute sample size estimates for intervention trials. We use these same pooled estimates of CIMTmax change in power calculations for the current study. Other assumptions include: =.05, a 20% difference in CIMT progression between abstinent participants (N = 300) and continuing smokers (N = 450), and use of the CIMTmax measure with an estimated change in CIMT for continuing smokers of 5.28 m (SD= 5.0 m).288 Based on these assumptions, we will have power of .81 to detect a 20% difference in progression between abstinent and smoking participants. This is a conservative power estimate as control variables should reduce error and our N is likely to exceed 750, and the projected effect size is smaller than that reported by Howard et al.1 Thus, we believe that the current study is adequately powered to detect predicted differences in CIMT progression over three years for the comparison of smokers versus continuously abstinent ex-smokers. Analyses of continuous measures of post-quit smoking also may yield greater power.

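### Aim 1 and Hypothesis 1 predict arrest or reversal of atherosclerosis, but the CIMT test described and powered can only show slower progression than in continuing smokers

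*Protocol*

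**What the plan says.** **The claim.** Specific Aims, goal 1: "We hypothesize that cessation will be followed by an arrest or reversal of atherosclerosis". Hypothesis 1 (Analytic Plan, Principal Hypotheses) says that cessation will be associated with reversal or arrest as measured by CIMT. The Background (Life After a Quit Attempt – Physiologic Outcomes) goes further. It describes earlier data as showing arrest over three years and adds that "we believe that more careful assessment of other risk factors may reveal" regression.

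**The analysis.** Hypothesis 1 codes abstinence either dichotomously or continuously and says "Baseline CIMT scores will be used to determine change". The model-building text says "Change will be modeled via entry of pretreatment (baseline) measures of the dependent variable and via change scores". CIMT is measured at baseline and Year 3 only, and Structural Models excludes it from the latent trajectory models for that reason.

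**The power.** The inputs are 300 abstainers, 450 continuing smokers, alpha .05, a change of 5.28 in continuing smokers, SD 5.0, and a 20% difference in progression. On these, "we will have power of .81 to detect a 20% difference in progression between abstinent and smoking participants". Under the same Power heading, the study that the Background cites for arrest is said to have found a current-versus-past-smoker difference of 7.3, "equivalent to a 20% difference in progression".

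**The concern.** Arrest means no further thickening in people who quit, and reversal means thinning. Both are statements about the sign of the abstainers' own mean change. A contrast with smokers answers a different question: whether abstainers thicken less than smokers do. That can be true while abstainers continue to thicken.

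The protocol gives no numerical meaning to arrest or reversal and names no criterion for the abstainers' change. At stake is what Aim 1 may conclude. The Background says that evidence of arrest could alter how clinicians treat tobacco dependence and could motivate smokers to quit. Slower progression is a weaker message than arrest.

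**Working it through.** **Inputs (Power section).** Change in smokers 5.28; SD 5.0; 300 abstainers; 450 smokers; alpha .05 (sidedness not stated); relative difference 20%. The unit symbol is lost in the text and is read here as micrometres; the argument does not depend on it.

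**1. Reproduce the stated power.**
- Difference = 0.20 × 5.28 = 1.056.
- SE of the difference = 5.0 × √(1/300 + 1/450) = 0.373.
- Two-sided power ≈ Φ(1.056/0.373 − 1.96) = .809, against the stated .81. A one-sided test would give .883, so the plan evidently used two sides.

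**2. What the planning effect implies for abstainers.** Assumption: the SD of 5.0, which the protocol gives beside the smokers' change, also applies to abstainers.
- Mean = 0.8 × 5.28 = 4.22.
- SE = 5.0/√300 = 0.289.
- Expected 95% CI = 4.22 ± 1.96 × 0.289 = 3.66 to 4.79, with the mean 14.6 SE above zero.
- If the abstainers' SD were 10 instead, the half-width would be about 1.13 and the interval about 3.09 to 5.35, still well above zero.

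**3. Smallest significant contrast.** 1.96 × 0.373 = 0.73, or 14% of 5.28. With smokers at 5.28, the contrast reaches significance with abstainers still at 5.28 − 0.73 = 4.55.

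**4. If arrest were true.** With zero change in abstainers the difference is 5.28 and the power of the contrast is about 1.00. The .81 is therefore a statement about slowing.

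**5. Annual or three-year figures.** The pooled estimates are described as annual rates, so 5.28 may be per year. If the mean and SD are both tripled, power stays at .81 and abstainers progress by 3 × 4.22 ≈ 12.7 over three years. The conclusion is the same.

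**6. What the 300 abstainers could show about arrest or reversal.** With SD 5.0 the 95% half-width is about 0.57. There is 80% power to show a true mean regression of (1.96 + 0.84) × 0.289 ≈ 0.81 (15% of 5.28), or, if the true change is zero, to exclude progression above about 0.81. With SD 10 these become about 1.13 and 1.62.

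**7. The cited study.** If 7.3 is 20% of the current smokers' progression, current smokers progressed by 7.3/0.20 = 36.5 and past smokers by 36.5 − 7.3 = 29.2. If the base is past smokers, they progressed by 36.5. Either way the Power section describes continued progression in past smokers, while the Background describes arrest.

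**The case against.** Several points on the other side stand.

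- Sizing a study for a smaller effect than the one hoped for is ordinary, and the protocol calls its power estimate conservative. The interval of 3.66 to 4.79 restates a planning input and does not forecast the result. Even so, the Power section also calls this effect the projected one, so the mismatch with the hypothesis is in the protocol's own words.
- The Power section labels its contrast accurately, as a difference in progression between smokers and continuous abstainers. It does not claim .81 power for arrest or reversal.
- A reader might infer that a significant contrast will be reported as arrest or reversal, and that the main conclusion of Aim 1 would then be wrong. No passage states such a rule. The protocol only leaves the reading open.
- The abstainers' signed mean change can be computed from the planned scans, and the protocol says that its list of analyses is not exhaustive. A statistical analysis plan, not available here, may add the estimate. That would not alter the wording of the aim and hypothesis, or the two accounts of the cited study.
- Aim 1 concerns effects of cessation and Hypothesis 1 speaks of association, so both are partly comparative. A one-group change in self-selected abstainers cannot separate cessation from ageing or measurement drift over three years. The smoker comparison remains the better evidence for a cessation effect.
- On the cited study, the reported difference is covariate-adjusted, the base of the 20% is not stated, and the source is not at hand. One cannot say which section is wrong, only that the two do not agree.

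**Conclusion.** The point holds as a mismatch between what is hypothesised and what is tested. The .81 is correct, but it is the power to show that abstainers progress less than smokers. In the scenario that yields it, abstainers still progress by about 4.22 (95% CI about 3.66 to 4.79), assuming SD 5.0 applies to them; doubling that SD or reading the figures as annual rates does not change the conclusion. A significant contrast alone therefore supports slower progression and leaves arrest and reversal undecided.

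It would go too far to call the design faulty or the sample too small. The contrast would have power near 1.00 if abstainers truly had no change, and 300 abstainers would estimate their own mean change to within about ±0.57 at SD 5.0. The shortfall lies in the wording and in the missing link between the claim and the estimate that could support it.

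**What to change.** - In Hypothesis 1, state that the abstainer-versus-smoker contrast tests slower progression and that the .81 applies to that contrast only. Keep it as the evidence for a cessation effect.
- Add the mean baseline-to-Year-3 CIMT change in continuous abstainers with its 95% CI. Use *reversal* only if the upper limit is below zero. Use *arrest* only if the upper limit excludes progression beyond a margin that the investigators set and justify in advance. The precision in step 6 of the working shows what size of margin the sample can resolve; it does not justify any particular value.
- If the investigators do not want these criteria, reword Aim 1 and Hypothesis 1 to slower progression than in continuing smokers.
- Reconcile the Background's description of the cited study (arrest) with the Power section's (a 20% difference in progression), after checking the source.

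**Cost.** Wording, plus one within-group estimate from scans already planned. Sample size, visits and measurements do not change. The arrest or reversal claim becomes harder to make.

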## Long-term smoking status and psychiatric morbidity. We predict that, compared to continuing smokers, abstinent ex-smokers will experience lower rates of occurrence of new psychiatric disorders during the 3-year follow-up. In one test of this hypothesis, we will use a composite measure of total incidence289 that combines mood, anxiety, and substance use disorders. Total incidence refers to disorder onsets (counting both new and recurrent cases) within a defined time period (e.g., 2 or 3 years). Power computation is difficult because to our knowledge, no population-based total incidence data for psychiatric disorders are available for smokers, ex-smokers, or never smokers. General population incidence rate data are available for certain psychiatric disorders (e.g., major depressive disorder, panic disorder) but these rates often exclude individuals with a past history of a given disorder (these are “initial incidence” rates) and the time frame is typically one year.

Although there are almost no data on total annual incidence of psychiatric disorders among quitting vs. continuing smokers (and hence, one reason for doing the proposed research), there are data that show incidence rates in the general population. An analysis of five Epidemiologic Catchment Area sites revealed a 1-year total incidence rate of about 12% for any diagnosis of affective, anxiety, or substance use disorders.93 However, we will be studying incidence over three years and the ECA data do not model the impact of recurrences. Perhaps the best data on 3-year incidence comes from De Graaf et al.290 These authors reported a 3-year incidence of 10% for initial diagnoses in those with no prior psychiatric diagnosis. We expect a higher incidence among nicotine dependent, continuing smokers given their higher rates of prevalence than nonsmokers (and hence higher rates than in the general population) and the majority of diagnoses tend to be recurrences.93,291 Regular smokers often have rates of psychiatric disorder that are 2-4 times the rates of nonsmokers (e.g., 292,293, and we expect their three-year total incidence rate to reflect that). We propose that continuing smokers will compile a 3-year incidence of 30% for affective, anxiety and alcohol diagnoses combined.93 We expect quitting to reduce 3-year incidence by about a third (a smaller effect size than was reported for a cessation-induced reduction of panic attacks.84 We believe such a decrease would be significant from a public health and clinical perspective.

Given the above assumptions, we predict that approximately 20% of abstinent participants and 30% of continuing smokers will develop a psychiatric disorder over the three-year post-quit period. Setting =.05, the current study has power of > .80 to detect a difference of this magnitude. Table 5 provides power estimates for various rates in the abstinent ex-smokers and 30% for the continuing smokers. As shown in Table 5, our group sample sizes provide sufficient power to detect a difference in rates as small as 9% (i.e., 30% versus 21%) with power of .79.

It is important to observe that the above power estimate does not take into account the impact of a prior diagnosis history covariate which should be significantly related to post-quit incidence. Also, we expect to have even greater power to detect change in continuous symptom measures since the one relevant study97 suggests a moderate effect size.

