a Vital signs includes carbon monoxide, blood pressure, weight, temperature, pulse, and height at Visit 2. b NCS-R-CIDI, which should last on average 90 minutes, includes a Screener and the following modules: Depression, Irritable Depression, Panic Disorder, Specific Phobia, Social Phobia, Agoraphobia, Generalized Anxiety Disorder, Suicidality, Use of Services, Alcohol Use, Tobacco Use, Chronic Conditions, Neurasthenia, 30-Day Functioning, 30-Day Symptoms, Obsessive-Compulsive Disorder, Worries and Unhappiness. c This will be administered to participants who are married or who have a domestic partner. d Blood will be drawn for the following tests: NMR lipid profile, creatinine, simultaneous fasting blood glucose and insulin, possibly carotenoids, hemoglobin A1C, and high-sensitivity c-reactive protein. e Smoking status includes a review of the abstinence calendar, nature of relapse contexts, use of cessation aids and new quit attempts.

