We plan to administer the following NCS-R-CIDI components: mental health (Depression, Irritable Depression, Panic Disorder, Specific Phobia, Social Phobia, Agoraphobia, Generalized Anxiety Disorder, Suicidality, Alcohol Use, Tobacco Use, Neurasthenia, Obsessive-Compulsive Disorder, Worries and Unhappiness, and 30-Day Symptoms), physical health and health quality of life (Use of Services, 30-Day Functioning, Chronic Conditions). Importantly, we are deleting a number of CIDI scales in the interest of reducing burden (e.g., all childhood disorder scales, eating disorders, gambling, demographics).

These scales will provide critical information on diagnosis and dimensional information on mental health, physical health, their impact on quality of life, and health & mental health care utilization. These NCS-R-CIDI measures will be supplemented with other measures to achieve a greater sense of status in critical domains.

*Psychometric status of additional instruments.* The instruments used in this study (see Table 4) all have psychometric properties that support the inferences for which they are being used. For instance, the MPQ brief form (MPQ-BF) has excellent psychometric properties as a personality measure.147 The Wisconsin Dependence Measure (WISDM-68) the Wisconsin-Probability of Relapse and Smoking Measure (WI-PRISM), and the Fagerström Test of Nicotine Dependence (FTND) have been shown to predict dependence outcomes such as relapse and withdrawal severity.138,156 In fact, there is a substantial literature attesting to the positive psychometric properties of all of the measures that will be used: e.g., the PANAS,274 the Quality of Life Inventory,275 the Depression Proneness Inventory (DPI),154,276 and so on. The psychometric properties of other, chief measures were discussed earlier.

Genotyping

DNA sequencing will take place at the University of Utah Huntsman Cancer Institute. It has four ABI 3700’s and one ABI3730 which can run a total of 28,000 sequence ladders per week. SNP typing will be performed by the ABI SNPlex system. This system can detect 4500 SNPs in parallel in as little as 15 minutes. Extensive capabilities also exist in this center for bioinformatics that enable investigators to collect and analyze DNA sequence, haplotype and SNP data. DNA extraction is described in Project 1.

Compensation

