The general approach we will adopt with dependent variables is as follows: when there are multiple measures of a type of dependent variable, we will examine the interrelations among the measures, determine the stability of findings across the class, and perhaps analyze a composite measure. For instance, with respect to *mental health* the NCS-R-CIDI yields categorical diagnoses and symptom counts. In addition it comprises measures of mental health quality of life, impact of mental health symptoms on daily functioning, and use of psychiatric services. We will explore how these different indicators are interrelated, and whether predictors bear similar relation to the different indicators. The latter will help us determine whether a finding is robust and stable. This strategy requires that we report findings across the different measures of common constructs. Finally, we may examine composite measures. For instance, in some analyses we plan to collapse across all major anxiety, affective, and substance use diagnoses (taking into account comorbidity). We plan to employ a similar strategy across the different major types of dependent variables that have multiple indicators: e.g., atherosclerosis, quality of life, nicotine dependence, alcohol use/abuse. For instance, alcohol variables will arise from time-line follow-back data, the Short Inventory of Problems, CIDI Diagnosis, and electronic diary data gathered in Project 1. Smoking relapse and calendar measures of smoking over each year will be produced using data generated by the time-line follow-back procedures used in follow-up interviews. This will produce measures of continuous abstinence, point-prevalence, and percent days smoking each year. Amount of smoking will be determined in each 7-day point prevalence period. Any of these could be used in analyses, but for modeling over time, percent days smoking over each year combined with heaviness measures should yield the most useful measures of tobacco exposure over time. Use of other tobacco or nicotine containing products will also be examined.

With respect to independent variables, we will use model-building procedures (described below) to systematically select best measures from a class, and also report prediction stability across measures.

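### The psychiatric composite is defined with substance use disorders but powered on alcohol only as its substance part; tobacco diagnoses are not excluded, so a literal reading makes the smoker-abstainer comparison partly circular

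*Protocol*

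**What the plan says.** The composite is described in three places in the protocol.

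- **Power, Long-term smoking status and psychiatric morbidity (definition).** One test of the hypothesis uses a total-incidence composite that "combines mood, anxiety, and substance use disorders". The event is defined as follows: "Total incidence refers to disorder onsets (counting both new and recurrent cases) within a defined time period".
- **Analytic Plan, Representing Constructs.** For some analyses, "we plan to collapse across all major anxiety, affective, and substance use diagnoses".
- **Same power subsection (rate assumption).** Continuing smokers are assigned a "3-year incidence of 30% for affective, anxiety and alcohol diagnoses combined". Abstainers are assumed to have about 20%.

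The interview content is listed twice. The Psychosocial part of the assessment section puts these modules under mental health: "Suicidality, Alcohol Use, Tobacco Use, Neurasthenia, Obsessive-Compulsive Disorder, Worries and Unhappiness, and 30-Day Symptoms". Footnote b to Table 4 has "Use of Services, Alcohol Use, Tobacco Use, Chronic Conditions". Neither list has a module for any other drug. The Psychosocial section also says that the interview produces DSM-IV diagnoses. No sentence leaves tobacco or nicotine diagnoses out of the composite.

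**The concern.** The first two places use a wider term than the third. Given the modules administered, the only thing that can separate substance use from alcohol is tobacco. The groups compared are continuing smokers and abstinent ex-smokers, and a continuously abstinent person can hardly acquire a tobacco diagnosis. Counting such diagnoses would put part of the exposure into the outcome, and the composite could differ between groups with no difference in mood, anxiety or alcohol disorders.

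The protocol guards against this kind of overlap for alcohol: Hypothesis 2 limits heavy drinking as a predictor to outcomes that do not contain alcohol diagnoses. It has no matching guard for tobacco, which is the exposure itself. The composite matters because it is the endpoint of one of only two power analyses in the plan.

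**Working it through.** **Inputs from the protocol (Power section).** 300 continuously abstinent and 450 smoking participants; alpha .05 (sidedness not stated; two-sided reproduces the plan); 30% in smokers; 20% or 21% in abstainers; stated power above .80 and .79 respectively. Table 5 is not shown in the text at hand, so only the figures quoted in the prose were checked.

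**Formula.** Two-proportion normal approximation with pooled variance under the null:

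power = Φ[(|p₁ − p₂| − 1.96·SE₀) / SE₁], where SE₀ = √[p̄(1 − p̄)(1/300 + 1/450)], SE₁ = √[p₁(1 − p₁)/300 + p₂(1 − p₂)/450], and p̄ is the weighted mean rate.

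**Step 1: the plan's own figures.**
- 21% v 30%: p̄ = .264, SE₀ = .0329, SE₁ = .0319; (.09 − 1.96 × .0329)/.0319 = 0.80; power .789. The plan states .79.
- 20% v 30%: p̄ = .260, SE₀ = .0327, SE₁ = .0316; (.10 − 1.96 × .0327)/.0316 = 1.14; power .872. The plan states above .80.

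The arithmetic is sound for the composite of affective, anxiety and alcohol diagnoses.

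**Step 2: what counting tobacco could do when cessation has no effect.** Assumptions, none of them given in the documents: 30% of both groups have a mood, anxiety or alcohol event; no abstainer has a tobacco event; a share q of smokers has a new or recurrent tobacco diagnosis, independent of the rest. The smoker rate is then 1 − (1 − .30)(1 − q), against 30% in abstainers.

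| q (assumed) | Smoker rate | Spurious difference | Chance of a significant result |
|---|---|---|---|
| 5% | 33.5% | 3.5 points | .17 |
| 10% | 37% | 7 points | .51 |
| 20% | 44% | 14 points | .97 |
| 30% | 51% | 21 points | >.99 |

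The spurious difference is .70q. It equals the plan's 10-point target when q = .10/.70, about 14%.

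**Step 3: after the fix.** Limiting the composite to mood, anxiety and alcohol leaves .789 and .872 as they are, because the 30%, 21% and 20% rates already refer to that composite.

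**The case against.** The strongest reply is that the power subsection settles the matter. It uses the broad term for the cited population data and then names alcohol when it sets this study's own rate. It also describes the smokers as nicotine dependent; if their existing tobacco diagnoses counted, 30% would make no sense. This stands as evidence of intent. It does not remove the conflict, because the two sentences that define the composite still use the wider term, and the Analytic Plan says all such diagnoses.

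Second, events are onsets, so dependence that persists from baseline would not clearly count. This stands, and it is why the table starts at 5%. Rates of 30% to 70% of smokers would be closer to a prevalence than to an onset rate. Recurrence after a quit attempt would still count under the stated definition.

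Third, a reader might infer that Hypothesis 2 would be confirmed by definition. The documents do not support that. The composite is one test among several: the Analytic Plan calls for reporting across measures of a construct, and Hypothesis 2 also uses symptom levels and considers internalizing diagnoses alone. Tobacco diagnoses enter none of these.

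Fourth, it is inferred that the Tobacco Use module yields a diagnosis that would enter the collapse, since some listed modules are not diagnostic. This is a fair caution.

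Finally, the exact list of diagnoses could be left to a statistical analysis plan. The point here, however, is that the protocol names the components and names them differently.

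**Conclusion.** The inconsistency is real and lies in stated endpoint text: the composite named for analysis is wider than the one that was powered, and the extra part can only be tobacco. The circularity is partial and conditional. The protocol does not say that tobacco diagnoses will be counted; it fails to exclude them, and its power text points to alcohol as the intent. Only this composite is exposed, and the sample size and power figures are unaffected.

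If the definition were followed literally, modest tobacco onset or recurrence in smokers would be enough to mislead: a false-positive chance of about .17 at 5% of smokers, .51 at 10% and .97 at 20%. These figures rest on the assumed tobacco rates, on independence from the other disorders, and on no tobacco diagnosis among abstainers. A reader might also infer that a spurious result is near certain; that holds only at the upper end of the assumed range.

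**What to change.** In the Analytic Plan (Representing Constructs) and in the power subsection on psychiatric morbidity, replace substance use with alcohol use in the definition of the composite. Add one sentence stating that tobacco and nicotine diagnoses are excluded from every mental health composite compared by smoking status. Both definitions then match the composite behind the 30% rate.

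The cost is a wording change in two places. No assessment, sample size or power figure changes, and the Tobacco Use module can still be administered and reported as a separate outcome.
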